### Outcome measurement

Outcomes will be measured at two-time points (within 1 week and after 3 months) for participants who complete baseline enrollment. Primary prognostic indicators included Lung function and 6MWT. Secondary outcome measures included mMRC, HRCT, and the questionnaire.

#### Assessments of basic characteristics

The patient will undergo lung function tests under the supervision of medical staff. TLC, VC, DLco, and min•mmHG are recorded in detail after the test [28, 29], while the lung function assessment table contains three levels (effective, stable, and ineffective) for qualitative assessment according to different values of TLC, VC, DLco, and min •mmHG.

The evaluation is based on the dyspnea scale (mMRC) developed by the British Medical Research Council [30]. The medical staff instructed the patients to complete the questionnaire according to protocol, and the patients are evaluated at the conclusion of the experiment. Each subject’s dyspnea level is meticulously recorded and categorized into three distinct categories. The severity of dyspnea increases as the dyspnea score rises.

#### HRCT of the chest

According to the 2018 New Evidence-based Guidelines for Diagnosis and Treatment of IPF [31], High-Resolution CT (HRCT) is the most important way to diagnose IPF at present [32]. The HRCT of the subjects before and after the trial is evaluated according to the “HRCT Efficacy Evaluation Table” and “HRCT Clinical Symptoms and Signs Efficacy Evaluation Table”. The evaluation criterion stated that the milder the lung lesions, the higher the HRCT score.

#### Exercise capacity tests

6MWT is mainly used to evaluate the severity and prognosis of heart and lung patients. The medical staff will introduce the test procedure to the patient and tell the patient to carry out the test after the patient calms down. Within 6 min, the patient began walking back and forth from the starting point. 15 s before the end of six minutes, the medical staff will inform the patient: “The test is coming to an end, please stand still when you hear stop.“ Borg grading is used after the test. 6WMT is divided into four grades according to the length of walking distance (300 m, 375 m, and 450 m as nodes). The longer the walking distance, the higher the grade. The Borg index (1–10) measures dyspnea or fatigue after a 6-minute walking test.

#### Questionnaires

The health-related quality of life (HRQoL) uses the St. George Respiratory Questionnaire (SGRQ) [33]. The SCRQ consists of 50 questions that are independently completed by the patient on the day of the Lung function examination, with no reminders and an observer checking for omissions. Each question has a predetermined score, and the weighted average calculation method will be utilized. The greater the score, the more severe the life consequences. Each part’s score is calculated, and the final score is obtained following processing.

### Criteria for discontinuing or modifying allocated interventions

We will seek consent from participants and conduct the trial after signing the informed consent form, and the individual wishes of the participants will be considered. If the participants do not consent and refuse to participate in the experiment, we will respect their views, postpone or alter the intervention, and report the exact reasons. The trial will be stopped if a participant is exposed to harmful conditions in the event of a possible or impossible adverse event or emergency (COVID-19 infection, acute exacerbation of illness, life-threatening situation). We will take proactive steps to provide appropriate treatment and care to patients who have adverse events during the trial.

### Statistical analysis

The SPSS (version 23.0) is used for data management and statistical analysis. The kolmogorov-Smirnov test is used for normality test. The normality data are expressed as mean ± SD, and the skewness data are expressed as median and quartile spacing. An intention-to-treat analysis will be used to assign participants whether or not they complete the intervention. Lost result data will be processed using a mixed-mode approach. Each protocol is then examined, including only patients who completed all outcome measures and followed the intervention protocol. Comparisons of baseline differences between groups will be made using one-way analysis of variance (ANOVA) or nonparametric tests. The training-related effects are evaluated using a 2 × 2 ANOVA (group × time). Differences in each group of variables over time (time effect, from baseline to 3 months) will be assessed using either a paired T-test or a nonparametric test. To detect differences between categorical variables, the Chi-square test will be applied. Bilateral *P* values < 0.05 are considered significant. In addition, the effects of different interventions on Lung function have been found in previous studies, and disease severity may be an important factor. Therefore, in order to investigate differences in effectiveness based on disease severity, a pre-designated subgroup analysis will be conducted.

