## Abstract

**Introduction:**

In this study, we will combine the traditional Baduanjin with Yijin Jing and Wuqinxi to create an optimized Baduanjin exercise program with three different forms (vertical, sitting, and horizontal) to adapt to idiopathic pulmonary fibrosis (IPF) patients in vairous stages of the disease. The purpose of this study is to explore and compare the therapeutic effects of this multi-form Baduanjin, traditional Baduanjin, and resistance training on lung function and limb motor function in IPF patients. The goal of this study is to prove a novel optimal exercise prescription strategy of Baduanjin exercise for improving and protecting lung function in IPF patients.

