## Methods

### Study design

This is a single-blind, randomized controlled clinical trial comparing (1) conventional care, (2) traditional Baduanjin (3) Modified Baduanjin (4) resistance training, (5) Modified Baduanjin, and resistance training. All the participants are from the Department of Respiratory Medicine, The First Affiliated Hospital of Jiangxi University of Traditional Chinese Medicine. On January 12, 2022, the protocol has been registered in the Chinese Clinical Trial Registry (ChiCTR2200055559). The study has been also approved on February 23, 2022, by the Ethics Committee of the First Affiliated Hospital of Jiangxi University of Traditional Chinese Medicine; the approval number is JZFYLL202202230011. All participants will sign informed consent forms in writing.

Subjects will be assigned according to a computer-generated table of random numbers and will be randomly assigned to 5 groups by an independent person who is unaware of the purpose of the experiment and the recruitment process. Sealed opaque envelopes are used to hide randomly assigned numbers to perform blinding. Considering that the intervention in this study has been performed in a motor manner, it is not possible to complete blinds for participants and therapists, so we included an outcome evaluator to keep the blinds going. The time points of the study are in Fig. 1 and the study procedure is shown in Fig. 2. The study protocol has been designed following the Standard Protocol Items: Recommendations for Interventional Trials (SPIRIT) guidelines [27].

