### Randomization and concealed allocation

Prior to the baseline assessment, participants will be randomized into five groups: CG, IG, TG, RG, and IRG. The allocation sequence will use “study randomized” transcendental prior distribution, the random number generator is (https://www.randomizer.org/) online random number generator, and the participation of participant recruitment assessment or not engage in the researchers. Concealed allocation will be achieved using sequentially numbered, sealed, and opaque envelopes kept in security cabinets that can only be opened by specifically authorized staff.

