#### Data analysis

The SPSS (version 23.0) is used for data management and statistical analysis. The kolmogorov-Smirnov test is used for normality test. The normality data are expressed as mean ± standard deviation, and the skewness data are expressed as median and quartile spacing. An intention-to-treat analysis will be used to assign participants whether or not they complete the intervention. Lost result data will be processed using a mixed-mode approach. Each protocol is then analyzed, including only subjects who completed all outcome measures and followed the intervention protocol. One-way analysis of variance (ANOVA) or nonparametric tests wil be used to compare baseline differences between groups. The effects of training are evaluated using a 22 ANOVA (group × time). Using either a paired T-test or a nonparametric test, differences in each group of variables over time (from baseline to three months) will be evaluated. To detect differences between categorical variables, the Chi-square test will be applied. P values less than 0.05 are considered significant.

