Resistance movement is characterized by setting relevant resistance movements for the relevant ten muscles, to improve the muscle strength and function of the relevant muscles, and to improve lung function and limb movement function. The Modified Baduanjin is a combination of whole-body aerobic exercise and breathing that can effectively improve dyspnea and limb movement ability. Consequently, we hypothesize that this combined exercise regimen may have a synergistic effect on IPF patients.

This study has several bright spots. First, the Modified Baduanjin is innovatively developed in three forms, standing, sitting, and horizontal, compared with traditional Chinese sports skills. As far as we know, the latter two forms are new forms that are not available in other exercise therapies. Therefore, patients with severe lung function injury, particularly long-term hospitalized patients, can choose the appropriate sitting or horizontal rehabilitation posture, which is not possible with other exercise therapies. Second, for IPF patients, we evaluate several comprehensive indicators of new-type Baduanjin on IPF in the stable phase, paying special attention to lung function and limb function. Third, a subgroup analysis of patients with different degrees of disease is conducted to study whether there are differences in the therapeutic effects of vertical, sitting, and horizontal types respectively, and finally to find out the best combination plan to optimize the therapeutic effect. Finally, this study is conducted strictly and standardized under CONSORT guidelines [34], to explore the therapeutic effect of Modified Baduanjin on stable IPF patients.

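### The efficacy test is written as a 2 × 2 (group × time) ANOVA, but five groups are randomised, so the between-arm comparisons are not defined

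*Protocol article*

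**What the plan says.** **Design.** Under Randomization and concealed allocation, "participants will be randomized into five groups: CG, IG, TG, RG, and IRG". Study design agrees that subjects "will be randomly assigned to 5 groups by an independent person". Under Outcome measurement, "Outcomes will be measured at two-time points (within 1 week and after 3 months".

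**Objective.** The Abstract's introduction sets out to "explore and compare the therapeutic effects of this multi-form Baduanjin, traditional Baduanjin, and resistance training on lung function" and limb motor function. That objective compares several active arms with one another.

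**Efficacy test.** Statistical analysis: "The training-related effects are evaluated using a 2 × 2 ANOVA (group × time". The Data analysis section repeats this as "The effects of training are evaluated using a 22 ANOVA (group × time". The multiplication sign has been lost there, so this is the same statement again and not a second error.

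**Other tests named.** One-way ANOVA (or a nonparametric test) is for baseline differences only. Paired tests are for change within a group, and chi-square is for categorical variables. The significance level is 0.05 throughout.

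**Missing data.** Intention-to-treat is stated, and "Lost result data will be processed using a mixed-mode approach". The Sensitivity analysis section adds multiple imputation.

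**Combination arm.** The Discussion adds: "we hypothesize that this combined exercise regimen may have a synergistic effect on IPF patients".

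**The concern.** The article does specify its efficacy test, and the test specified does not fit the design. With two group levels, the group × time interaction is a single contrast between two groups. Five arms can be brought into that form in several ways, and these answer different questions:

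- One pair of arms, which leaves three arms out.
- The four exercise arms pooled against control, which removes the comparison of modified Baduanjin, traditional Baduanjin and resistance training.
- Four tests against control, which omit modified versus traditional Baduanjin and modified Baduanjin versus resistance training.
- Ten pairwise tests, each at 0.05 with no overall test.

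The choice would be made after the data are in, and it can change the trial's conclusion. None of the other tests named compares the arms on follow-up values of a continuous outcome, so nothing else in the article fills the gap.

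**Working it through.** **1. The plan's own figure.** Inputs from Sample size: difference 54 m, SD 57 m, two-sided 0.05, power 80%.

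- Normal approximation: n = 2 × [57 × (1.960 + 0.842) / 54]² = 17.5, so 18 per group.
- Exact two-sample t-test: 18 per group gives 78.9% power and 19 gives 81.1%. The stated 19 reproduces.
- 30% loss: 19 / 0.7 = 27.1, which is 27 rounded or 28 rounded up; 5 × 28 = 140.

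The sample size therefore rests on one two-group comparison at 0.05.

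**2. Dimension of the test.**

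- 2 × 2: interaction df = (2 − 1)(2 − 1) = 1.
- Five groups at two times: (5 − 1)(2 − 1) = 4.
- Pairs among five arms: 5 × 4 / 2 = 10, of which 4 involve the control group.

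**3. Error rate if the 2 × 2 test is repeated at 0.05.** Chance of at least one false positive for one outcome when no arm differs:

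| Tests | Treated as independent, 1 − 0.95^k | Allowing for shared arms (simulated, 19 per arm) |
|---|---|---|
| 4 against control | 0.19 | 0.15 |
| 10 pairwise | 0.40 | 0.28 |

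The right-hand column is the one to use, because the tests share arms. It assumes equal arm sizes.

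**4. Precision.** With two time points, the two-group interaction is a comparison of change scores. Assume an SD of 57 m at both times and a correlation ρ between baseline and 3 months. The article gives no ρ, so it is varied.

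- SD of change = 57 × √[2(1 − ρ)].
- Baseline-adjusted (ANCOVA) SD = 57 × √(1 − ρ²).
- Variance ratio, ANCOVA to change = (1 − ρ²) / [2(1 − ρ)] = (1 + ρ)/2.

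| ρ (assumed) | SD, change | SD, ANCOVA | Variance ratio | Power at 19 per arm, change | Power at 19 per arm, ANCOVA |
|---|---|---|---|---|---|
| 0.3 | 67.4 | 54.4 | 0.65 | 67% | 85% |
| 0.5 | 57.0 | 49.4 | 0.75 | 81% | 91% |
| 0.7 | 44.2 | 40.7 | 0.85 | 96% | 98% |

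At ρ = 0.5 the change-score SD equals the planning SD of 57 m. From there upward, change scores reach the planned 80% power with 19 per arm. Below 0.5 they do not.

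**The case against.** **It may be a slip.** The factors are given as group and time, so 2 × 2 could be a misprint for 5 × 2. Pairwise testing would also fit a sample size built on a two-group difference, and nothing in the article suggests pooling. Lists of contrasts are often left to an analysis plan, which is not shown. This has force against any claim that the comparisons cannot be made: a series of pairwise 2 × 2 tests would make them. It does not remove the mismatch, because the article states a layout and that layout does not match its five arms.

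**Baseline is not ignored.** It enters as a time level, and comparing change scores is valid in a randomised trial. This stands. Adjustment is an efficiency choice, and its size depends on a correlation the article does not give.

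**Intention-to-treat.** A reader might infer that the ANOVA drops everyone without a 3-month value and so contradicts intention-to-treat, given the 30% loss allowed for. The article does not support that. It names a method for lost data and multiple imputation, and it limits the analysis to people with complete outcomes only in the separate per-protocol analysis. What remains is that the missing-data method is not tied to the stated test.

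**Synergy.** A reader might also infer that a required synergy test is missing. The hypothesis appears only in the Discussion and is worded tentatively. The obvious contrast, IRG − IG − RG + CG, would not isolate synergy either. By the Intervention sections, a combined session holds 20 minutes of each component, against 40 minutes in the single-component sessions.

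**Conclusion.** The mismatch holds and should be corrected: the efficacy test has two group levels and the trial has five arms. As written, the test leaves the between-arm comparisons undefined; it does not make them impossible. If the gap were filled by repeated testing at 0.05, the familywise error per outcome would be about 0.15 (four tests) to 0.28 (ten tests), assuming equal arms and no true differences.

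The loss of precision from change scores is secondary and not an error. It is 25% of the variance at ρ = 0.5 and 15% at ρ = 0.7, and power falls below plan only if ρ is under 0.5. No contradiction of intention-to-treat is shown.

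**What to change.** In both Statistical analysis and Data analysis, replace the 2 × 2 ANOVA with the following:

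- **Model.** One model for each continuous outcome with a five-level arm factor. Report the overall arm test, or the arm × time test on 4 df if both time points are outcomes.
- **Contrasts named in advance.** IG−TG, IG−RG and TG−RG for the stated objective; each exercise arm against CG; IRG−IG and IRG−RG for the combination.
- **Multiplicity.** State one rule for these contrasts, such as a fixed testing order or a stepwise adjustment. The list covers nine of the ten pairs, so the rule matters.
- **Baseline (recommended).** Adjust for the baseline value of the same outcome.
- **Missing 3-month values.** Handle them inside this analysis, by multiple imputation or by a repeated-measures mixed model with baseline among the outcomes. A mixed model whose only outcome is the 3-month value recovers nothing for a participant who lacks it.
- **Synergy.** Label any such contrast exploratory, because a combined session is not the sum of the two single-component sessions.

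**Cost.** Analysis wording only, dated before unblinding. Recruitment was already complete at submission and baseline values are collected, so no new data are needed. The real price is power under the multiplicity rule. With the planned 54 m, SD 57 m and 19 per arm, a Bonferroni correction leaves 62% power per comparison for four tests and 48% for ten, before any gain from baseline adjustment. That favours a short, ordered list of primary contrasts.

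### The only post-baseline between-arm test of continuous outcomes is written as 2 × 2 for a five-arm trial and names no comparison; if it is run as an omnibus test, only within-arm paired tests give arm-level results

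*Protocol article*

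**What the plan says.** The trial has five arms: "participants will be randomized into five groups: CG, IG, TG, RG, and IRG". The abstract gives the aim as to "explore and compare the therapeutic effects of this multi-form Baduanjin, traditional Baduanjin, and resistance training". The Discussion adds a comparison of resistance exercise with modified Baduanjin, a synergy hypothesis for the combined arm, and single against joint programmes. These are questions about particular pairs of arms.

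For continuous outcomes after baseline, the Statistical analysis section lists two procedures:

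- Between arms: "The training-related effects are evaluated using a 2 × 2 ANOVA (group × time"). The Data analysis section repeats this, with the multiplication sign missing from the printed text.
- Within each arm: the before-after difference, labelled a time effect, "will be assessed using either a paired T-test or a nonparametric test". The Data analysis section repeats this as well: "Using either a paired T-test or a nonparametric test, differences in each group of variables over time".

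For categorical variables the plan says: "To detect differences between categorical variables, the Chi-square test will be applied". The one-way ANOVA is reserved for baseline differences. A single threshold of P < 0.05 covers everything. Neither section names an arm-to-arm contrast or a reference arm, and neither marks the within-arm tests as descriptive.

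**The concern.** A group × time ANOVA with five groups and two time points is 5 × 2, so the stated 2 × 2 does not describe this trial. Two readings are possible, and neither fixes the comparisons.

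- As one omnibus test over five arms, a significant interaction says that the arms do not all change alike, but not which arm differs from which. The paired tests then become the only listed tests on continuous outcomes that yield a P value for a named arm.
- Taken literally, two arms at a time, it is a randomised comparison. However, five arms give 5 × 4 / 2 = 10 possible pairs, and the plan does not say which of them count.

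A before-after P value in one arm does not use the randomisation. It combines any treatment effect with familiarity with the walking test, regression to the mean, disease course and co-interventions. The last are real here: every arm attends the course described under Advice to stay active, and every arm gets at least weekly phone contact (Adherence to interventions). If one arm's paired test is significant and another's is not, that does not show that the two arms differ. The risk is that arms with the same true change are reported as if one worked and another did not.

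**Working it through.** **1. The plan's own figure.** Inputs from the Sample size section: difference between groups 54 m, SD 57 m, two-sided 0.05, power 80%.

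- Normal approximation: n = 2 × (1.960 + 0.842)² × 57² / 54² = 17.5, rounded up to 18 per arm.
- Two-sample t-test: 18.50, rounded up to 19, with power 81.1% at 19 per arm.

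The stated 19 is reproduced. It is the size for one randomised two-arm comparison, so the design is sized on a between-arm difference.

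**2. Setting for the within-arm tests.** From the document: 19 completers per arm, SD 57 m, five arms, two-sided 0.05. Assumed, because the document gives neither: a before-after correlation r, and a true gain g that is the same in every arm, so that no arm differs from another.

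**3. Formulas.**

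- SD of change = 57 × √(2(1 − r)). At r = 0.7 this is 57 × √0.6 = 44.2 m, and the standard error is 44.2 / √19 = 10.1 m.
- p = probability that one paired t-test is significant (noncentral t, 18 degrees of freedom, noncentrality g / 10.1).
- Probability that some of the five arms are significant and others not = 1 − p⁵ − (1 − p)⁵.

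**4. Results at r = 0.7.**

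| Common true gain | p per arm | Mixed result across arms |
|---|---|---|
| 5 m | 0.075 | 32% |
| 10 m | 0.155 | 57% |
| 20 m | 0.464 | 93% |
| 30 m | 0.800 | 67% |
| 40 m | 0.962 | 18% |

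The formula peaks at p = 0.5, where it gives 1 − 2 × 0.5⁵ = 93.75%, so the 20 m row is close to the worst case.

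**5. Sensitivity to r at a 20 m gain.** 83% at r = 0.5, 93% at 0.7, 89% at 0.8 and 41% at 0.9. Both assumptions matter: at 30 m and r = 0.8 the figure is 31%.

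**6. No change in any arm.** 1 − 0.95⁵ = 22.6% chance that at least one arm is significant, for each outcome.

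**7. The randomised test on the same data.** A simulation of 20,000 trials per setting (19 per arm; r = 0.5, 0.7 or 0.8; common gain 0, 15 or 30 m) ran the five-arm group × time test beside the paired tests. With a common 15 m gain, at least one exercise arm was significant while the control arm was not in 47% to 53% of trials. With no change this was 17% to 18%, and with 30 m it was 7% to 40%. The five-arm group × time test rejected in about 5% of trials in every setting.

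**The case against.** A reader might infer that the arms will be judged on before-after significance instead of on randomised comparisons. The document does not support that. The sentence directly before the paired test assigns training effects to the group × time ANOVA, whose interaction compares change between randomised groups. The paired test is labelled a time effect, and nowhere does the article say that efficacy will be concluded from it. The sample size also rests on a between-group difference. All of this stands.

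It is also fair that a literal 2 × 2 ANOVA would be a two-arm randomised comparison, so the within-arm tests are the only arm-level tests on the omnibus reading alone. Named post hoc contrasts are commonly left to an analysis plan, which is not shown here, so their absence would be no finding by itself.

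Finally, the percentages depend on an assumed gain and correlation, and they arise only if paired results are compared across arms. This stands too, and it is why the full spread is shown.

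Two things are not answered. The stated ANOVA does not fit the stated number of arms. And inferential within-arm tests are written into the plan under the same P < 0.05 as everything else. Both are in the text itself, so an analysis plan would have to override them, not merely add detail.

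**Conclusion.** The point holds in a limited form. The plan contains a randomised comparison, but specifies it in a shape that does not fit five arms and two time points and that leaves the arm-to-arm comparisons unidentified. Beside it stand five within-arm tests per outcome, with nothing to mark them as descriptive. On the omnibus reading these are the only listed tests on continuous outcomes that speak for a named arm.

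If they were used to rank arms that truly change alike, a mixed pattern would appear in 18% to 93% of trials over common gains of 5 to 40 m. This rests on 19 completers per arm, SD 57 m and r = 0.7, with the gain and r assumed. The 22.6% figure with no change needs neither assumption. These figures describe the danger of relying on the paired tests; they do not forecast what the investigators will do.

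**What to change.** Replace the 2 × 2 ANOVA with one five-arm model of the 3-month value adjusted for baseline. Name the between-arm contrasts that carry the conclusions: each exercise arm against CG, IG against TG, and IRG against IG and against RG. State that every efficacy statement rests on these contrasts. Report within-arm change only as mean change with 95% CI, without P values. Use one wording in both the Statistical analysis and Data analysis sections.

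The cost is wording in the analysis plan. The Trial status section says recruitment is complete, but the same data serve, and the change can be made before unblinding. Fewer significant results could be quoted.

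Naming several contrasts also exposes a limit of the sample size, which covers one comparison. If, as an assumption, Bonferroni were applied to the four contrasts with CG (0.05 / 4 = 0.0125), an unadjusted t-test at 19 per arm would have 61.6% power for 54 m, against 81.1% for a single comparison. Baseline adjustment would recover some of this, depending on the correlation.

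### Chi-square is the only test named for categorical variables; if it is used to compare mMRC and the lung-function levels between arms, it discards their order and some power

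*Protocol article*

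**What the plan says.** The Statistical analysis section, repeated almost word for word under Data analysis, assigns tests as follows.

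- Baseline differences between groups: one-way ANOVA or nonparametric tests.
- Training effects: "The training-related effects are evaluated using a" group × time ANOVA.
- Change over time within a group: "will be assessed using either a paired T-test or a nonparametric test".
- Categorical variables: "the Chi-square test will be applied".

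No list says which variables count as categorical. A nonparametric test is offered for the baseline comparison and for within-group change, but not for a between-group comparison at three months.

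Two graded outcomes are defined under Assessments of basic characteristics. mMRC dyspnoea is "categorized into three distinct categories", and the text says that a higher score means worse dyspnoea. The lung-function table "contains three levels (effective, stable, and ineffective) for qualitative assessment". Under Exercise capacity tests, 6MWT is also cut into four grades with "300 m, 375 m, and 450 m as nodes", a longer distance giving a higher grade. Outcome measurement makes lung function and 6MWT primary and mMRC secondary.

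**The concern.** Each of these grades has an order that the protocol itself states or that its labels imply. Pearson chi-square gives the same result if the categories are shuffled, so it does not use that order. A shift of patients towards better grades is then harder to detect than it need be. A significant result also does not say in which direction an arm moved.

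The arms are small and, according to Trial status, recruitment is complete. A larger sample can no longer make up for an inefficient test, but the choice of test can still be improved.

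**Working it through.** **1. Sample size available.** The Sample size section gives a 54 m difference, SD 57 m, two-sided 0.05 and 80% power.

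- Standardised difference: 54/57 = 0.947.
- Normal approximation: n = 2 × [57 × (1.960 + 0.842)/54]² = 17.5, rounded up to 18.
- t-based: 18.50, rounded up to **19**, which matches the stated figure.
- Allowing for 30% loss: 19/0.70 = 27.14. The protocol states 27; rounded up it is 28, and 5 × 28 = 140, the stated total.
- Completers per arm: 27 × 0.70 = 18.9, or 140 × 0.70/5 = 19.6.

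So about 19 per arm applies to completers, and 28 per arm is the upper end if every randomised patient contributes.

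**2. Which stated rule reaches which outcome.**

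| Outcome form | Stated between-group method that fits |
|---|---|
| 6MWT in metres | group × time ANOVA |
| TLC, VC, DLco as values | group × time ANOVA |
| mMRC as a score | group × time ANOVA could be used |
| mMRC in three categories | chi-square, by elimination |
| Lung-function levels | chi-square, by elimination |
| 6MWT in four grades | chi-square, by elimination, if tested at all |

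**3. Why order matters.** For two arms and three levels, Pearson chi-square has (2 − 1)(3 − 1) = 2 degrees of freedom, and the rank test has 1. For five arms they are (5 − 1)(3 − 1) = 8 and 4. A shift along the order is spread over more degrees of freedom with chi-square.

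**4. Size of the loss for three-level outcomes.** The documents give no grade distribution, so these are assumptions. With a control split of 30/40/30 and a common odds ratio of 4:

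- Middle or better: odds 0.70/0.30 = 2.333; × 4 = 9.333; probability 9.333/10.333 = 0.903.
- Best level: odds 0.30/0.70 = 0.429; × 4 = 1.714; probability 1.714/2.714 = 0.632.
- Split in the other arm: about 10/27/63.

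The second set of assumptions is a normal variable cut into equal thirds in the control arm and shifted by a stated number of SDs. Simulated power at two-sided 5%, two arms, Pearson chi-square without correction against a rank test:

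| Setting (assumed) | n per arm | Chi-square | Rank test | Loss (points) |
|---|---|---|---|---|
| 30/40/30, odds ratio 4 | 19 | 47% | 58% | 11 |
| 30/40/30, odds ratio 4 | 28 | 66% | 76% | 10 |
| Thirds, shift 0.5 SD | 19 | 20.2% | 26.6% | 6.4 |
| Thirds, shift 0.8 SD | 19 | 44.1% | 55.4% | 11.3 |
| Thirds, shift 0.947 SD | 19 | 58.3% | 68.8% | 10.5 |
| Thirds, no shift | 19 | 4.8% | 4.6% | – |

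For an overall five-arm comparison with assumed odds ratios of 1, 2, 4, 2 and 4 and 19 per arm, power is 40% with chi-square and 52% with Kruskal-Wallis, a loss of 12 points. With no shift, both tests reject at about the nominal 5%, so the loss is not explained by a difference in error rate.

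**5. The powered comparison.** 6MWT in metres with 19 per arm, 54 m and SD 57 m has 81% power by t-test. The chi-square sentence does not touch this.

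**The case against.** The strongest objection is that the protocol never sends these grades to chi-square. The sentence would fit sex and other baseline characteristics just as well, mMRC is also described as a score, and assigning a test to each secondary variable is often left to a fuller document. This stands as a limit on the point, which is therefore conditional. It does not remove the point: baseline comparisons have their own sentence, chi-square is the only method named for categorical variables, and no between-group rank or ordinal method is named for the three-month data.

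A reader might go further and infer three things that the documents do not support.

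- **That the primary 6MWT comparison is weakened.** On the four 6MWT grades the loss is indeed larger: 51–53% with chi-square against 72–74% with a rank test, for a 54 m shift, 19 per arm and assumed control means of 350 to 400 m. However, the trial is sized on metres, metres can go to the ANOVA, and the text names no test for the grades. The same holds for TLC, VC and DLco as recorded values.
- **That all the graded analyses ignore baseline.** Effective, stable and ineffective read as a rating of change, although the protocol does not define them. If so, baseline is already used. The objection about baseline applies to mMRC only.
- **That the proportional-odds model would gain exactly these amounts.** The power figures are for rank tests; the model was not simulated.

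The lack of direction in a significant chi-square is shared by an overall Kruskal-Wallis test across five arms. That part of the concern is met only by named pairwise comparisons or by odds ratios.

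**Conclusion.** The point holds in a limited form. The only rule stated for categorical variables is a poor match for mMRC in categories and for the lung-function levels, if these are compared between arms under it. The cost is roughly 5 to 12 points of power for three levels at 19 to 28 per arm. That range rests on assumed grade distributions and assumed shifts, since the documents give neither. Every non-null setting examined showed a loss. The sized 6MWT comparison and the continuous lung-function measures are unaffected, so this is an inexpensive improvement to the analysis of graded outcomes and not a threat to the trial's main comparison.

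**What to change.** In Statistical analysis, and in the duplicate text under Data analysis:

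1. State which variables chi-square covers, and limit it to unordered ones such as sex.
2. Compare mMRC and the lung-function levels between arms with an ordinal method. This can be Kruskal-Wallis with Wilcoxon tests for named pairs, or proportional-odds regression with arm as a factor, reporting odds ratios with 95% confidence intervals for the named contrasts.
3. If the regression is used, adjust for baseline grade for mMRC only. Outcome measurement provides two time points, so a baseline grade should exist. The lung-function levels appear to rate change already; the text should say so.
4. Analyse 6MWT in metres and show the four grades descriptively.

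The cost is one or two sentences and no extra data. The regression adds a proportional-odds assumption; name the rank test as the fallback if the model does not fit. Because recruitment is complete, the choice should be fixed and dated before anyone sees outcome data by arm.
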